#### Engagement Measures

To examine changes in task-related engagement in different training conditions, a multilevel modeling analysis will be conducted. The time point (level 1 units) will be nested within participants (level 2 units). The variable time will have 6 levels (ie, after sessions 1, 2, 3, 4, 5, and 6). A model-building procedure [84] will be used to build the most parsimonious model to test the hypotheses, using the AIC to identify the most appropriate model. The model will be computed using maximum likelihood estimation. To analyze the impact of gamification on interest and enjoyment, a 1-way analysis of variance will be performed. Missing values will be handled using multiple imputations.

Regarding behavioral engagement, Kaplan-Meier survival curves [85] will be calculated to assess the time at which attrition occurred in each training condition and compared statistically using a log-rank test. Participants will be classified as noncompleters if they do not complete all 6 training sessions. Finally, a 1-way analysis of variance will be performed to determine whether there are differences in the mean number of sessions completed between the training conditions.

#### Cognitive Measures

To determine changes in attentional bias and interpretation bias in the different training groups, multilevel modeling analyses will be conducted. For each model, the time point (level 1 unit) will be nested within participants (level 2 units). The variable time for each cognitive measure will have 2 levels (ie, pre- and posttraining), with pretraining as the reference point. The control group (control ABMT) will serve as a reference group for comparisons between the groups over time. A model-building procedure [84] will be used to build the most parsimonious model to test the hypotheses, using the AIC to identify the most appropriate model. All models will be computed using maximum likelihood estimation. In addition, Pearson correlations will assess the relationship between changes in attentional bias magnitude from pre- to posttraining and changes in scores on symptom measures (ie, pain intensity, pain interference, anxiety, and depression).

#### Perceived Improvements

To determine changes in perceived improvement in the different training groups, a multilevel modeling analysis will be conducted. The time point (level 1 units) will be nested within participants (level 2 units). The variable time will have 2 levels (ie, posttraining and 1-month follow-up), with posttraining as the reference point. The control group (control ABMT) will serve as a reference group for comparisons between the groups over time. A model-building procedure [84] will be used to build the most parsimonious model to test the hypothesis, using the AIC to identify the most appropriate model. The model will be computed using maximum likelihood estimation.

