### Aims and Hypotheses

The aim of this study is to investigate the effects of a gamified web-delivered ABMT intervention in a sample of adults with chronic musculoskeletal pain via a randomized, double-blind, placebo-controlled trial. To do this, 3 ABMT conditions will be directly compared: nongamified sham control ABMT, nongamified standard ABMT, and gamified ABMT. It is hypothesized that the gamified ABMT condition, relative to both the standard ABMT and control ABMT conditions, will rate more highly on self-reported engagement (ie, task-related engagement, enjoyment, and interest) as well as complete more training sessions and have less dropout. On the basis of the findings from the broader ABMT literature and theoretical considerations [20-22], it is expected that the standard ABMT and gamified ABMT conditions will show a reduction in pain-related attentional biases and interpretation biases after training sessions, with the largest reduction in the gamified ABMT condition. Furthermore, it is expected that both the standard ABMT and gamified ABMT conditions, relative to the control ABMT condition, will show reductions in pain intensity, pain interference, anxiety, and depression scores immediately after training and 1-month later and that these reductions will be greater in the gamified ABMT condition compared with the standard ABMT condition. Finally, it is expected that both the standard ABMT and gamified ABMT conditions, relative to the control ABMT condition, will report global pain-related improvements following training and that these improvements will be larger in the gamified ABMT condition compared with the standard ABMT condition.

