##### Perceived Improvement

Participants’ perception of overall pain-related improvement following training will be assessed using the Patient Global Impression of Change (PGIC) scale [66]. This measure comprises a single item rated on a 7-point Likert scale, ranging from 1 (*very much improved*) to 7 (*very much worse*), with *no change* in the middle of the scale (4). For descriptive purposes, participants will be classified into 3 categories according to the PGIC score: disease deterioration (0-3 points), stable disease (4 points), or disease improvement (5-7 points) since the start of the program [67]. The PGIC has been recommended by the Initiative on Methods, Measurement, and Pain Assessment in Clinical Trials [68] and is widely used in chronic pain research [67,69].

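### The PGIC analysis is worded as a comparison of change between posttraining and 1 month, which does not test the hypothesis about how much improvement each arm reports

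*Protocol article*

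**What the plan says.** All references are to the protocol article.

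- **Aims and Hypotheses.** Both active arms, relative to control, "will report global pain-related improvements following training and that these improvements will be larger in the gamified ABMT condition" than in the standard condition. This is a statement about the level of reported improvement in each arm.
- **Perceived Improvement (Secondary Outcome Measures).** The participant's "perception of overall pain-related improvement following training will be assessed using the Patient Global Impression of Change (PGIC) scale", and the descriptive categories refer to change "since the start of the program". Table 1 lists the PGIC at posttraining and at 1 month only.
- **Perceived Improvements (Statistical Methods).** "To determine changes in perceived improvement in the different training groups, a multilevel modeling analysis will be conducted". Then: "The variable time will have 2 levels (ie, posttraining and 1-month follow-up), with posttraining as the reference point". Then: "The control group (control ABMT) will serve as a reference group for comparisons between the groups over time". The model is to be the most parsimonious one by AIC, fitted by maximum likelihood, to test the hypothesis. No coefficient or contrast is named.
- **Symptom Measures and Cognitive Measures.** These use the same sentence about the control group, but with pretraining as the reference time.

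**The concern.** In the symptom and cognitive models the reference time precedes treatment, so the group-by-time term is the treatment effect. The PGIC section keeps that wording but moves the reference to a post-treatment visit. Group-by-time then asks whether the arms drift differently after training has ended, not whether they report different improvement.

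An analyst who reads the term that carries the effect in the other models would find nothing when a benefit lasts, and would find a significant result when a benefit is lost. Because the deciding term is not named, the choice could also be made after the data are seen. The outcome is secondary, but it is the only one in which participants judge their overall improvement directly.

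**Working it through.** The article gives no effect size, power or correlation for the PGIC, so there is no stated figure to reproduce.

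**Step 1: what each term means.** Let A = 1 for an active arm (0 = control) and T = 1 for the later visit (0 = reference visit):

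E[Y] = b0 + b1·A + b2·T + b3·A·T

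Suppose training produces a benefit of size D.

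| Model | Reference time | Pattern of benefit | b1 (arm) | b3 (group-by-time) |
|---|---|---|---|---|
| Symptom scores | pretraining | D at the later visit | 0 in expectation, by randomization | D |
| PGIC | posttraining | D at both visits | D | D − D = 0 |
| PGIC | posttraining | D at posttraining, 0 at 1 month | D | 0 − D = −D |

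For the PGIC, the hypothesis in Aims and Hypotheses concerns b1 (posttraining) and b1 + b3 (1 month), or their average. It does not concern b3 alone. Gamified versus standard is the difference between two arm coefficients, and control-referenced coding does not print it directly.

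**Step 2: inputs for an illustration.**
- From the article: two-sided alpha 0.05; target 40 per arm; planned minimum 30 per arm; about 30% dropout, so 40 × 0.70 = 28 per arm.
- Assumed: arm means of 0, 0.45 and 0.90 SD (control, standard, gamified). The 0.45 step borrows the effect on pain interference quoted in Sample Size Estimation. Within-person correlation is 0.5 or 0.7, with a random intercept, normal ratings and complete data.
- 4,000 simulated three-arm trials per setting, at 28, 30 and 40 per arm.

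**Step 3: how often each test is significant** (range over both correlations).

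| Test | Benefit lasts, 28-30 per arm | Benefit lasts, 40 per arm | Benefit gone by 1 month, 28-40 per arm |
|---|---|---|---|
| Group-by-time | 4.6-5.8% | 4.8-5.6% | 87-99.8% |
| Arm, at posttraining | 84-88% | 95% | 85-96% |
| Arm, averaged over visits | 91-95% | 98-99% | 35-53% |

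The roughly 5% in the first row follows from b3 = 0 and holds for any constant benefit. The other figures depend on the assumed effects. They are three-arm tests with a 0.90 SD spread. A single pair of arms 0.45 SD apart, compared at posttraining, has 39% power at 28 per arm and 52% at 40.

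**Step 4: what AIC would select** among time, time + arm, and time × arm.

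| Scenario | time + arm | time × arm | no arm term |
|---|---|---|---|
| Benefit lasts | 81-87% | 13-15% | 0.2-3% |
| No benefit | 11-13% | 6% | 81-83% |

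With a large lasting benefit, AIC usually drops the interaction and keeps the arm term, so the benefit is visible if that term is read. With no benefit it usually drops the arm term too, and then the selected model gives no between-arm estimate or interval to report.

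**Step 5: direction of the scale.** The Perceived Improvement section runs the item from 1 (very much improved) to 7 (very much worse). It then classes 0-3 as deterioration and 5-7 as improvement: "or disease improvement (5-7 points) since the start of the program". The two directions are opposite, and 0 is not on the scale. Until they are reconciled, the sign of any PGIC contrast cannot be read.

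**The case against.** A reader might infer that the planned analysis cannot detect a lasting benefit, or that it will report one as null. The article does not support that. It never says that group-by-time decides the question, and it says the model is built to test the hypothesis, which is about level. With control and posttraining as references, the arm coefficients are the active-versus-control differences at posttraining. If AIC drops the interaction, they are the differences averaged over both visits. Step 4 shows that this is the usual outcome under the assumed lasting benefit. This part of the objection stands.

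It can also be said that *changes* is loose template language: Engagement Measures uses it for a rating with no pretraining value. And naming the tested coefficient is often left to an analysis plan that is not shown here. This stands only in part. An unnamed contrast alone would be no finding. But the article does fix an aim, a reference time and a form of between-arm comparison for the PGIC, and the only comparison it puts into words does not match its own hypothesis. The identical sentence in the symptom and cognitive sections makes the group-by-time reading the natural one.

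The 5% figure follows by construction once a constant benefit is assumed. It describes that contrast and is not a power loss built into the plan. Nor would a fading benefit have to look like harm: the same model shows the posttraining arm effect beside the interaction, and the sign is unsettled in any case (Step 5).

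**Conclusion.** The defect is a mis-worded comparison with no named test, in a model that can answer the question. Read as worded, the PGIC comparison is zero for a lasting benefit and does not address the hypothesis in Aims and Hypotheses. Read through the arm term, the same model does address it.

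The algebra needs no assumption beyond the coding the article states. The detection rates in Step 3 and the AIC frequencies in Step 4 are illustrative, because they rest on assumed effects and correlations and on complete data. The point concerns one secondary outcome and should be corrected before analysis.

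**What to change.** In the Perceived Improvements section under Statistical Methods:

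1. State that the hypothesis is tested by the between-arm differences in PGIC level at posttraining and at 1 month, or by their average. Choose one in advance, and list gamified versus standard alongside each active arm versus control.
2. Keep the arm terms in the model regardless of AIC, so that an estimate and interval are always reported.
3. Report group-by-time only as a description of durability.
4. Speak of differences in perceived improvement in place of changes in it.

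In the Perceived Improvement section under Secondary Outcome Measures, reconcile the item's anchors with the three descriptive categories before any contrast is interpreted.

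The cost is wording only: the data, visits and model are the same, with a different contrast named as the test.

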#### Exploratory Analyses and Subgroup Analyses

Additional exploratory and subgroup analyses will be performed to explore the role of engagement metrics (ie, number of training sessions completed) and individual differences (ie, attentional control, pain-related worrying, personality characteristics, and recruitment setting [clinical vs nonclinical]) in the impact of training conditions on the primary outcomes. These analyses will be conducted using appropriate statistics and are subject to the final sample size and power.

### Ethics and Dissemination

This trial has been approved by the human research ethics committees of the Royal Brisbane and Women’s Hospital and Queensland University of Technology and registered on the Australian New Zealand Clinical Trials Registry, ACTRN12620000803998, version 1.0, approved on August 10, 2020. All participants will provide informed consent electronically before inclusion in the trial. Of note is that participants will not be provided information about the 3 training conditions (ie, control ABMT, standard ABMT, and gamified ABMT). They will be informed that the aim of the study is to test whether a novel psychological program can reduce chronic pain and improve pain-related health outcomes and that they will be randomly assigned to either receive the intervention or complete a similar task (the control group). In doing so, participants will remain blinded to their allocation, as it would be easy to realize whether they are in the *active* gamified group or not (and noting that the control group does not include game-like features). Participants will be debriefed at the conclusion of their study involvement. Participants who received the intervention will no longer have access to the computerized task. Participants in the control ABMT condition will be offered the opportunity to perform the standard ABMT training. No data will be collected, used, or analyzed during that time. At the completion of the final session, the participants will no longer have access to the intervention.

Any modifications to the study protocol will be recorded and communicated with the human research ethics committees and the clinical trial registry. The final data set will be accessible to approved members of the research team. The results of this trial will be reported in the form of a doctoral research thesis (for [name]) and published in a peer-reviewed journal and presented at conferences. No professional writers will be used. A lay summary of the outcomes and results of the study will be made available to the participants.

## Results

Ethics approval for this study was granted by the human research ethics committees of the Royal Brisbane and Women’s Hospital in April 2020 and Queensland University of Technology in September 2020. Study recruitment commenced in August 2021 and is ongoing. Data collection and analysis are expected to be concluded by October 2022 and January 2023, respectively. The results of this study are expected to be published in mid-2023.

## Discussion

### Study Contributions

This protocol describes a randomized, double-blind, placebo-controlled trial aimed at evaluating the effects of a gamified web-delivered ABMT intervention on pain intensity, pain-related outcomes, cognitive biases, behavioral and self-reported engagement, and perceived improvement in a sample of adults with chronic musculoskeletal pain. The use of gamification in such programs may have the potential to keep participants engaged and motivated in the sustained and repeated use of the task as well as increase retention.

To our knowledge, this is the first study to evaluate the effects of gamification techniques in a pain ABMT intervention. This study will provide important information on the potential therapeutic benefits of gamified pain ABMT programs and shed light on the motivational influences of certain game elements in the context of pain. If results support its effectiveness, this novel, web-delivered, easy-to-administer cognitive program could open new avenues for alleviation of pain suffering, thereby improving the quality of life for these individuals and their families. This is especially significant considering that chronic pain affects between 19% and 31% of the population worldwide [86-88]. Finally, the expected findings will provide novel contributions to the knowledge base and understanding of chronic pain. This, in turn, may open new directions for therapeutic interventions.

### Strengths and Limitations

This study has significant strengths. First, findings from the 3-arm randomized controlled trial design, with the inclusion of a nongamified version of the intervention, will allow us to determine whether the addition of game elements leads to increased motivation, engagement, and intervention efficacy. Further strengths of the study include (1) the rigorous, well-designed, and prespecified study protocol that has been reported as per SPIRIT [23] guidelines and preregistered on a clinical trial registry; (2) the use of an empirically supported set of pain-relevant word stimuli; (3) the inclusion of self-report and behavioral measures of engagement as a primary outcome; (4) the large chronic pain sample drawn from clinical and nonclinical settings; and (5) the inclusion of a 1-month follow-up assessment.

Despite its strengths, this study also has limitations. First, although restricting our sample to individuals with chronic musculoskeletal pain strengthens the methodology of the study, this may limit the generalizability of the results to other types of chronic pain conditions. However, at this early stage in investigating the impact of game elements on ABMT, we believe that the advantages of researching a homogeneous sample outweigh the benefits of a heterogeneous sample. Second, the current ABMT approach provides limited control over the environment under which ABMT will be completed, which could potentially affect the results. However, again, the use of a web-based delivery mode was an informed choice. There is an increasing need and demand in society for remote delivery and access to health treatments, which has been highlighted by the current COVID-19 pandemic [89] and isolation environment and is also of particular benefit to those living in regional and remote areas. With the move to web-based administration and the resulting reduction in face-to-face interpersonal interaction, there may arguably be an even greater need for these interventions to include features such as gamification to facilitate engagement and continued motivation to self-administer such tasks. Finally, the use of the dot-probe task will only allow us to provide a static snapshot of the dynamic attentional process that unfolds over time [6]. Currently, web-based measures investigating how attentional dynamics resolve over time are not yet widely accessible; therefore, we opted for the dot-probe assessment paradigm, as it is frequently used in web-based attentional bias research [9].

## Abbreviations

ABMT: attentional bias modification training
ACS: Attentional Control Scale
AIC: Akaike information criterion
BAS: Behavioral Activation System
BIS: Behavioral Inhibition System
CONSORT: Consolidated Standards of Reporting Trials
GCPS: Graded Chronic Pain Scale
PCS: Pain Catastrophizing Scale
PGIC: Patient Global Impression of Change
PROMIS: Patient-Reported Outcomes Measurement Information System
RT: reaction time
SPIRIT: Standard Protocol Items: Recommendations for Interventional Trials
